### Sources of bias

Selection bias at recruitment will be avoided by separating the processes of determining patient eligibility and treatment allocation and by using random permuted blocks overseen by the CTU, not allowing physiotherapists assessing and treating patients to predict the next allocation in their clinic. Trial participants will know they are having physiotherapy-led exercise and brief details about the three interventions (see Additional file
1 PIS). It is not possible to blind physiotherapists but they will deliver treatment to participants in only one of the three intervention groups. A PCRN nurse blind to treatment allocation will obtain informed consent and oversee the collection of baseline and follow-up questionnaire data, and will collect minimum data over the telephone where necessary. An evaluation of the success of nurse blinding procedures will be completed and a procedure for reporting incidents where blinding has been compromised will be in place.

Data entry, coding, security, storage and management will follow the standard operating procedures in the CTU at Keele University. Data enterers will receive training in line with CTU procedures and will be blind to the identification of the three intervention groups. Random 10% data entry accuracy checks will be conducted at regular intervals, data accuracy will be audited and accuracy rates recorded. The trial statistician (EN) will remain blind until after the creation of a locked analysis dataset at 18 months follow-up and the completion of the primary and secondary analyses.

Comparing available variables between consenting and non-consenting individuals, trial participant withdrawals and completers will be carried out to evaluate external validity. All participants will be free to withdraw from the trial at any time without having to give any explanation. Where possible, we will collect information about the reasons for withdrawal from the trial. Using validated outcome measures will reduce measurement error. Treatment will be recorded by physiotherapists in standardised formats and audits of these case report forms will be undertaken throughout. Feedback to physiotherapists delivering the interventions will be provided, where necessary, so they can modify and improve the delivery of the interventions. Each intervention is supported by a specific protocol and documentation, developed for the BEEP trial and previously tested in the pilot study.

### Interventions

The interventions will be delivered in participating physiotherapy centres in up to 6 NHS Primary Care Trusts (PCTs). All patients will receive an advice and information booklet (which will include information about the value of specific lower limb and general exercise and simple self-help messages such as the use of analgesics, and home heat therapy for pain relief, see Additional file
2 for a copy of the advice booklet) and a home exercise programme. Different physiotherapists delivered each of the three interventions. Each of the three intervention groups are detailed below with supporting explanation and justification (see Table 
1 for a summary of the interventions). They are all examples of complex interventions as they involve a number of separate but interacting components that are likely to be important to the success of the intervention
[40]. Whilst the key outcomes are knee pain and disability, the interventions are all behaviour change interventions focused on exercise and physical activity behaviour change.

**Table 1 T1:** Summary of the BEEP trial interventions

**Key features**	**Usual physiotherapy care**	**Individually tailored exercise**	**Targeted exercise adherence**
**Number of sessions**	Up to 4 sessions	6 to 8 sessions	8 to 10 sessions
**Time period of treatment**	Up to 12 weeks	Up to 12 weeks	Up to 6 months
**General education**	Advice and information booklet	Advice and information booklet	Advice and information booklet
**Exercise focus**	Focus on lower limb exercise	Focus on lower limb exercise	Focus on both lower limb and general exercise. Signposting and support to engage in general physical activity opportunities in local community
**Individualisation**	Exercises selected from a pre-printed, standardised written template	Exercises individually prescribed for each patient, supported by an individualised, written exercise programme	Exercises individually prescribed for each patient, supported by an individualised, written exercise programme
**Progression**	Minimal progression	Good progression	Good progression
**Supervision**	Minimal supervision	Good supervision	Good supervision
**Exercise monitoring**	No exercise diary	Exercise diary	Exercise and physical activity diaries
**Provision of follow-up**	No follow-up after 12 weeks	No follow-up after 12 weeks	Follow-up and monitoring contacts (telephone or face to face) through to 6 months

All participants may continue to access usual primary care in addition to BEEP treatment. This may include ongoing or new medications, further healthcare consultations with other health professionals, referrals for imaging and surgical opinion and these co-interventions will be recorded on participants’ follow-up questionnaires. For the purposes of the trial, physiotherapy services will contact participants who fail to attend their treatment sessions up to three times in order to try to (re)engage the participant in BEEP treatment sessions. Hydrotherapy, group-based sessions, acupuncture and intra-articular injections will not be permitted in any of the BEEP trial treatment protocols. Intervention fidelity will be assessed through audits of treatment data collected in trial-specific case report forms (comparing these data with the intervention protocol and with the physiotherapy clinical records). We will collect data on the number and content of BEEP treatment sessions using physiotherapy case report forms in all three treatment groups and use those data in our interpretation of the trial results.

### Intervention 1: usual physiotherapy care

Usual physiotherapy care consisting of advice and exercise is the most appropriate control group for the BEEP trial given that randomised trials
[15] and systematic reviews
[6] consistently show that interventions that include exercise are superior to those which do not. We are not using an attention control group as this trial is designed explicitly as a pragmatic trial, building on evidence about the effectiveness of exercise interventions. Clinical practice guidelines
[2] recommend that all patients with OA are advised to exercise and in UK clinical practice, patients are seen in relatively few treatment sessions, and provided with brief relatively standardised exercise programmes that do not take into account differences between individual patients. Our ABC knee study described usual UK physiotherapy practice and formed the basis for the BEEP trial protocol for usual care
[14].

The BEEP trial protocol for usual physiotherapy care will consist of advice and lower limb exercise previously tested and shown to be more effective in the short-term than advice alone
[15]. Exercises will be selected from an agreed template of commonly prescribed exercises (printed from the commonly used PhysioTools computer software), including specific lower limb muscle strengthening (non-weight-bearing and weight-bearing) and range of movement or stretching exercises. Patients will receive up to 4 one-to-one treatment sessions with a physiotherapist over a period of 12 weeks, during which advice to continue to exercise will be provided but individualisation, progression and supervision of the exercise programme will be minimal, as in usual care. Other interventions used frequently by physiotherapists such as manual therapy and electrotherapy will be permitted as per usual care and they will be recorded on case report forms but the emphasis of the intervention will be supporting the patient to self-care and to follow the advice and exercise programme at home. This usual care protocol matches usual UK practice in that it focuses on lower limb strengthening exercise, relies on self-report rather than the use of exercise diaries to monitor adherence and progress, is delivered over few treatment sessions and thus has limited opportunity for individualisation, supervision or exercise progression and does not offer refresher or booster sessions following the end of the episode of care
[14].

### Intervention 2: individually tailored exercise (ITE)

Standardised exercise programmes such as those used in the usual physiotherapy care group in the BEEP trial do not take into account differences between individual patients. Consequently, individuals will be working at relatively different intensities, which for some may be too little to get a training effect, and for others may be too difficult. To be optimally beneficial, exercise should be progressed so that appropriate physical stress is placed upon the individual for further improvements to be obtained
[40]. Exercise self-efficacy (confidence to exercise despite the knee pain) has been identified as a predictor of exercise behaviour in many populations
[41,42]. Supervision of exercise can enhance patients exercise self-efficacy and self-regulatory skills and reassure them that they can perform the exercises. It also provides good opportunity to reassure the patient about pain responses to specific exercises or to change the exercise prescription to ensure optimal performance or more tolerable pain response. Lack of adequate individual tailoring, supervision and progression of the lower limb exercise programme may in part explain the small benefits seen in some previous exercise trials. Our previous trial results
[15,19] suggested that a lower limb exercise programme that was supervised and progressed over six treatment sessions resulted in greater improvements in pain than one provided over an average of four sessions. Therefore the protocol for Individually Tailored Exercise was developed to ensure the prescription of an individualised, supervised and progressed lower limb exercise programme.

The BEEP trial protocol for Individually Tailored Exercise will consist of a supervised individually tailored and progressed exercise programme. The aim of the intervention is to initiate and progress an individually tailored exercise programme, which is supervised in clinic, practiced at home and progressed in terms of intensity over 12 weeks. The intervention is modelled on a previously successful exercise intervention from one of our previous trials
[19], and focuses on individualised strengthening (non-weight-bearing and weight-bearing), stretching and balance exercise for lower limb rehabilitation and functional task training. The patient and physiotherapist will define lower limb functional and exercise goals and agree targets that are reviewed and progressed. Individualisation is based on the findings of the physiotherapy assessment of each individual, including biomechanical and physiological observations, pain responses to specific exercises and starting levels of strength, range of movement and balance. Exercises will be prescribed for each individual and participants will be given their own individual print-out of their specific exercise prescription (selected and printed from PhysioTools computer software) and these exercise prescriptions (and print-out instructions) will change over time as the exercise programme is progressed. Physiotherapists will encourage exercise behaviour change using self-monitoring through use of an exercise diary to record their adherence with their lower limb exercise prescription (see Additional file
3). In order to provide greater opportunity for individualisation, supervision and progression of exercise, patients will receive between 6 to 8 one-to-one treatment sessions with a physiotherapist. There will be no scheduled follow-ups (refresher or booster sessions) with the physiotherapist beyond 12 weeks.

### Intervention 3: targeted exercise adherence (TEA)

Adherence to long-term treatment regimes, particularly those involving behavioural components such as exercise, is consistently lower than adherence to medication
[43]. Exercise adherence, irrespective of exercise type, may be a key factor determining the success of exercise. In a previous trial of exercise for this patient population, we observed high exercise adherence rates in the short-term through to the end of treatment at 12 weeks, which fell to just over 50% at 12 months
[19]. Long-term adherence to lower limb exercise is perhaps unrealistic as these can be challenging to incorporate into daily routines and individual lifestyles and many patients do not consider them enjoyable, stopping them once symptoms reduce or resolve. It may be more realistic to target general physical activities that individuals have previously engaged in and enjoyed (since previous exercise behaviour is theoretically the strongest source of self-efficacy information
[41], or physical activities that individuals have positive expectations about (since these positive expectations may increase exercise intentions and ultimately exercise behaviour) in order to support engagement in and adherence to exercise. Our previous ABC knee study
[28] highlighted the many different barriers and facilitators to exercise and physical activity, and that no single exercise type or exercise setting is acceptable to all. Thus we designed this Targeted Exercise Adherence intervention to include an adherence-enhancing ‘toolkit’ of optional tools and techniques for physiotherapists to use with different participants, based on their assessment of individual participants and early feedback from participants (See Additional file
4 for summary of contents of the toolkit). The content of the intervention was directly informed by the results of our Cochrane systematic review
[26] and a networking meeting, supported by Arthritis Research UK, during which national experts and patient advocates agreed the intervention. Whilst the general physical activity identified and encouraged by physiotherapists will be individualised for participants, we anticipate that many may choose walking as it is seen as inexpensive and accessible. Pedometers have been shown to increase physical activity
[44] and to increase step counts in older people
[45] and therefore we will include pedometers within the suite of options for physiotherapists to give participants who wish to target increases in walking activity.

The BEEP trial protocol for Targeted Exercise Adherence will begin with a focus on the lower limb (as in the Individually Tailored Exercise group) but transitions to focus increasingly on general physical activity adherence over time. In addition to prescribing an individualised, progressed and supervised lower limb exercise programme, physiotherapists will assess patients’ current general physical activity levels, their intentions to increase their physical activity levels, their attitudes to exercise for knee pain and general health and explore their individual barriers and potential facilitators to exercise. This group will receive 4 treatments up to week 12 and a further 4 to 6 contacts from week 12 through to 6 months (a total of 8 to 10 treatment contacts). In the first 4 treatments, the aim will be for participants to initiate and progress an exercise programme with supervision that will include lower limb and general exercise, and to identify (with the support of the physiotherapist) general physical activity opportunities within the local community that are suitable for, and interest, the individual. Pro-active follow-up from the physiotherapist will take place from week 12 through to 6 months, using choices of telephone and face-to-face contact, providing an additional 4 to 5 contacts with each participant. The aim is to enhance long-term exercise adherence, promote increased general physical activity and encourage participants to develop an exercise ‘habit’, shifting the focus away from lower limb exercise in the earlier treatment sessions and towards sustainable lifestyle changes in physical activity in later treatment sessions. The follow-up sessions will ascertain and promote exercise adherence, increases in physical activity levels, support patients to integrate exercises into their activities of daily living, allow repetition and amendment of the exercise programme based on individuals’ experiences or concerns and progression at a pace suitable for the individual. The adherence enhancing ‘toolkit’ contains different educational and behavioural tools for facilitating physical activity behaviour change, selected for use based on an individualised assessment of each patient. As our Cochrane review identified that no one model of behaviour change was superior for facilitating adherence to exercise for chronic musculoskeletal pain, different theoretical models have underpinned the development of the toolkit, including self-efficacy
[42] and self-regulation theory
[46]. Tools will include self-monitoring through use of exercise and physical activity diaries (See Additional file
5), SMART goal-setting (specific, measurable, achievable, realistic, time-related) to facilitate the translation of intention into physical activity behaviour, reminders, corrective feedback and reinforcement, behavioural contracting for physical activity
[47], pedometers to support increases in walking, example templates to discuss and generate an individual exercise set-back plan, and information about (with active support to access) local physical activity opportunities and facilities in the community. The target by the end of the 6 months period is that participants are engaged in physical activity opportunities within their locality and have had support from the physiotherapist to overcome initial problems or barriers in engaging in these activities. The emphasis is therefore on maintenance of physical activity beyond the period of support from a health professional and NHS-based programme.

### Physiotherapists delivering the interventions

Up to 50 physiotherapists in the participating services will be trained and supported to deliver one of the three BEEP trial interventions. A training programme has been developed and tested in the pilot study and consists of a stepped training course as follows: physiotherapists delivering usual care will attend the first day only, those delivering Individually Tailored Exercise will attend the first day plus a further two days of training (total of three days of training) and those delivering Targeted Exercise Adherence will attend the first three days plus a further two days (total of five days of training). On-going support to adhere to the treatment protocols will be offered through PCRN physiotherapy research facilitators who have also undertaken the BEEP training programme and who will conduct regular audits of physiotherapy case report forms to investigate treatment fidelity. All physiotherapists will be invited to evaluate the training programme through completion of brief questionnaires before and directly following their training and at the end of treatment of all BEEP trial participants (approximately 18 months later). Further workshop refresher sessions to support BEEP physiotherapists will be provided during the course of the trial. The full details of the content and justification for the training programme and the observed changes in physiotherapists’ attitudes, beliefs and intended behaviours through the use of case vignettes will be provided in full in a separate publication.

### Outcome measures

#### Primary outcomes

This trial has two primary outcomes, lower limb pain and function measured using the Western Ontario and McMaster Universities Osteoarthritis Index (WOMAC)
[48], collected at baseline and all follow-up time-points (3, 6, 9, 18 and 36 months). The primary time-point is 6 months after randomisation. The psychometric properties of the WOMAC
[48] have been extensively studied in knee pain populations in clinical trials of different interventions including exercise
[49] and the WOMAC has been recently shown to be the most responsive of five pain measures
[50]. The pain subscale ranges from 0 (no pain) to 20 (maximum pain) and the function subscale ranges from 0 (no disability) to 68 (maximum disability). It is particularly suitable for the BEEP trial as it specifically captures self-reported pain during activities and the degree of difficulty with everyday physical activities, both of which are key treatment targets of physiotherapy-led exercise.

#### Secondary outcomes

A range of secondary outcomes will be collected: the proportion of treatment responders using the internationally agreed Outcome Measures in Rheumatology Clinical Trials (OMERACT-OARSI) clinical responder criteria
[16,17] that combines data on pain and function from the WOMAC
[48] with patient’s global assessment of change (recorded using a 6 point Likert Scale); physical activity levels (Physical Activity Scale for the Elderly (PASE) which assesses physical activity levels over a 1-week period combining physical activity from several domains including household, occupational and leisure
[51]); self-reported body mass index (calculated from self-reported height and weight); exercise adherence (attendance at treatment sessions, self-reported adherence to prescribed exercise programme); use of local physical activity facilities in the previous 7 days (single item); a modified version of a measure of treatment acceptability and credibility
[52,53]; a measure of illness perceptions (Brief Illness Perceptions Questionnaire
[54]); confidence in ability to exercise (Self-efficacy for Exercise Scale
[55]); outcome expectations from exercise (Outcome Expectations for Exercise Scale 2
[56]); anxiety (Generalised Anxiety Disorder Assessment 7
[57]); depression (Personal Health Questionnaire Depression Scale
[58]); self-reported health care resource use (both NHS and private health care); and overall health status (EQ-5D-3 L
[59]). Resource use and EQ-5D-3 L data will be used in the cost-utility analysis (further details are provided in the ‘Economic analysis’ section).

#### Accelerometry outcomes

Physical activity will also be measured in a subsample of participants (a target of n = 30 from each group), through snap-shots of 7-day accelerometry at each follow-up time-point. Accelerometers are motion sensors worn on the hip and will be used in this trial to estimate physical activity as counts per minute, time spent in light, moderate and vigorous physical activity and proportions of people who meet guideline levels of physical activity
[60]. Accelerometers will be allocated at the point of randomisation. The accelerometer units will be posted out to the participants with full instructions. Participants will be asked to wear the unit during waking hours for 7 consecutive days and then to post the unit back to the research centre where the data collected will be downloaded and analysed. During the trial, accelerometers will be allocated at regular intervals (approximately monthly) to the next three participants randomised to each treatment group. A random allocation procedure will not be used, as not all participants will be willing to wear them. A regular accelerometer allocation procedure is needed to enable accelerometers to be available to collect data for all 90 participants (at baseline and follow-up) from a pool of 30 accelerometers available for the trial. The allocation procedure will be phased in at the start of the trial to ensure that the system is running smoothly and that accelerometers are being returned in time to be reused by other participants. Those who do not return their accelerometers will be posted a written reminder.

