#### Randomisation and allocation concealment

Following receipt of a signed consent form and baseline questionnaire, the BEEP trial administrator will randomise the participant using a computer-generated randomisation schedule provided by the Musculoskeletal Clinical Trials Unit (CTU) at Keele University, password-protected to ensure that research nurses and trial statisticians remain blind to treatment allocation. Participants will be individually randomised to one of the three treatment groups using random permuted blocks of size 3. To ensure that patients at each physiotherapy clinic have a chance of receiving any of the interventions, randomisation will be stratified by physiotherapy clinic. Following randomisation, the trial co-ordinator will liaise with the appropriate physiotherapy clinic to arrange the first appointment for each trial participant. The patient will then be informed in writing of the date, time and location of their first appointment in the physiotherapy clinic. The GP of each trial participant will be sent a letter to confirm that their patient is taking part in the BEEP trial. Thus our procedures ensure baseline data are collected prior to randomisation, that the allocation is concealed until after the patient has been recruited into the trial and until the moment of randomisation and that the person assigning participants to intervention groups (study administrator) has no involvement in the eligibility screen, consent or treatment processes.

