#### Analysis of accelerometer data

Accelerometry data from the subsample of BEEP trial participants will be analysed using ActiGraph (version 6) accelerometer software. Prior to analysis, data will be cleaned by excluding time periods containing more than 60 minutes of zero count (where it is assumed the accelerometer is not being worn) and by including only those participants who have worn the accelerometer for at least 5 days for 10 hours or more. Sensitivity analyses will be conducted by changing the threshold to exclude minutes of zero count from 60, to 30 and 90 minutes respectively with the later threshold recommended for participants with knee pain
[72]. For each participant we will generate the following at each data collection point: number of valid minutes, counts per minute, proportion of time spent at each level of physical activity, using the cut-offs from Freedson et al
[73]. We will also calculate the proportion of participants meeting exercise/physical activity recommendations
[60].

Descriptive statistics will be given for the accelerometer variables at baseline and by treatment arm. Change (between baseline and each follow-up time point) in the average count per minute and in the proportion meeting the exercise recommendations will be analysed using analysis of covariance (ANCOVA) and logistic regression respectively with analyses adjusted for the covariates defined for the clinical effectiveness analysis and by treatment arm.

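### Month-0 accelerometry is recorded after randomisation and may overlap the first treatment session, yet the accelerometer analysis adjusts for it as a baseline

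*Protocol article*

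**What the plan says.** Under Accelerometry outcomes, the protocol article states: "Accelerometers will be allocated at the point of randomisation". It adds that "accelerometers will be allocated at regular intervals (approximately monthly) to the next three participants randomised to each treatment group". Delivery is by post: "The accelerometer units will be posted out to the participants with full instructions". On wear: "Participants will be asked to wear the unit during waking hours for 7 consecutive days". The same section explains that the schedule is needed "to collect data for all 90 participants (at baseline and follow-up) from a pool of 30 accelerometers available for the trial", and Table 2 lists accelerometry at month 0 as well as at every follow-up.

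The section on randomisation and allocation concealment concludes: "Thus our procedures ensure baseline data are collected prior to randomisation". It also says that the trial co-ordinator arranges the first clinic appointment once the participant has been randomised. It does not give the interval to that appointment and does not mention accelerometer wear.

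Under Analysis of accelerometer data, the quantity analysed is "Change (between baseline and each follow-up time point) in the average count per minute", using ANCOVA. The proportion meeting activity recommendations is analysed by logistic regression. Both are adjusted for the covariates of the clinical effectiveness analysis, and that list includes the baseline value of the outcome concerned.

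**The concern.** A baseline covariate is safe to adjust for because treatment cannot have altered it. A recording made after randomisation lacks that guarantee. If activity in one arm has begun to shift during the wear week, part of the effect sits in the covariate and the adjustment removes some of it. When the early shift has the same direction as the later effect, the bias is towards no difference.

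Accelerometry is the only device-based measure of physical activity in the trial, and Table 2 marks it as a clinical effectiveness outcome. Targeted Exercise Adherence aims directly at physical activity: general exercise and the search for local opportunities belong to its first four treatments. A wear week that runs into early treatment could therefore move differently between arms. The subsample has no power calculation behind it, so there is little room to lose part of an effect.

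**Working it through.** **Step 1: order of events.** A unit goes "to the next three participants randomised to each treatment group". The arm is therefore already assigned when a unit is given out. Posting and a 7-day wear follow. No reading of this sequence places the month-0 week before randomisation. The general statement on baseline data is true of the postal questionnaire, which is returned before randomisation, but not of accelerometry.

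**Step 2: position relative to treatment.** The appointment is arranged after randomisation, and so is the posting of the unit. The article sets no order between the wear week and the first session. Overlap is neither excluded nor established.

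**Step 3: effect on the planned estimate.** The plan gives no figure to reproduce here. Let D be the true arm difference at follow-up, f the share of D already present at month 0, and b the within-arm slope of follow-up on month 0 (b = r when the SDs are equal).

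- Follow-up as outcome, adjusted for month 0: D - b × fD = D(1 - b × f).
- Change as outcome, adjusted for month 0: the slope becomes b - 1, so the estimate is (D - fD) - (b - 1) × fD = D(1 - b × f), the same result.
- Change without adjustment: D(1 - f). This is not the planned analysis.

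The values of r and f are assumptions. The loss under the planned analysis is r × f:

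| r | f = 0.10 | f = 0.25 | f = 0.50 |
|---|---|---|---|
| 0.3 | 3% | 7.5% | 15% |
| 0.5 | 5% | 12.5% | 25% |
| 0.7 | 7% | 17.5% | 35% |

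A simulation of 400,000 records with r = 0.5 agreed. The adjusted estimate kept 1.000, 0.875 and 0.750 of D at f = 0, 0.25 and 0.50. With a true pre-randomisation baseline, f = 0 and the whole effect is recovered. The formula covers mean counts per minute, not the logistic outcome.

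**Step 4: would adjusting for PASE be a better main analysis?** PASE is collected before randomisation. Assume a standardised effect of 0.35 (the trial's design value for WOMAC, borrowed here), 30 per arm, and a correlation of 0.3 between PASE and accelerometry.

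- PASE-adjusted: SE = √(2/30 × (1 - 0.3²)) = √(2/30 × 0.91) = 0.25, no bias.
- Planned, r = 0.7, f = 0.5: bias = 0.35 × 0.35 = 0.12; SE = √(2/30 × 0.51) = 0.18; root mean squared error 0.22.
- Planned, r = 0.5, f = 0.5: bias = 0.25 × 0.35 = 0.09; SE = √(2/30 × 0.75) = 0.22; root mean squared error 0.24.

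In both cases the planned analysis has the smaller total error. PASE adjustment therefore suits a sensitivity analysis rather than a replacement.

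**The case against.** The strongest reply accepts the timing and disputes what follows from it.

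- **Knowledge of allocation.** A reader might infer that participants know their arm while wearing the unit. The documents do not show this. The letter sent after randomisation is said only to tell them when and where to attend. Participants cannot be blinded, but the article does not say when they learn their arm. This objection stands.
- **Selection by arm.** A reader might also infer that willingness to wear a unit differs by arm, so that the subsample is no longer a randomised comparison. The article says that not everyone will be willing, but not when they are asked. Without evidence that participants know their arm, arm-dependent refusal remains a possibility only. This stands too.
- **Early divergence may be small.** Every arm receives a booklet and a home exercise programme, and Targeted Exercise Adherence starts with lower-limb work before moving towards general activity. Values of f near 0.50 may be too high. That is fair, and is why the range goes down to 0.10.
- **A loss of 25% to 50%.** This would follow from an unadjusted change score with f of 0.25 to 0.50. The plan adjusts for month 0, so these figures do not describe it.
- **Article-level detail.** Scheduling wear against the first visit might be left to the full protocol. The order of randomisation and month-0 wear, however, is stated in the article and conflicts with its own general statement. That part of the objection does not remove the point.

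**Conclusion.** The point holds in limited form. Month-0 accelerometry follows randomisation, contrary to the general statement on baseline data, and the analysis treats it as a baseline covariate with no stated safeguard against overlap with treatment. If an early shift occurs in the direction of the later effect, the planned estimate of mean counts loses r × f of its size: 3% to 35% for the assumed ranges, and nothing if no shift occurs.

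The scope is the accelerometry outcomes in about 90 participants. The questionnaire baselines, including WOMAC and PASE, are collected before randomisation, so the primary outcomes are untouched. A reader might infer that the accelerometer comparison is certainly biased or has lost its randomised basis. The documents support neither: overlap with treatment, knowledge of arm during the wear week and arm-dependent willingness are all open possibilities. This is a cheap improvement, not a threat to the trial's main conclusions.

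**What to change.** 1. Record willingness to wear an accelerometer before randomisation, take consecutive willing consenters, and complete the 7-day wear week before randomising them.
2. If that is not feasible, require the wear week to end before the first physiotherapy session and before the arm is disclosed.
3. If month-0 wear stays after randomisation, restrict the statement in the randomisation section to questionnaire data.
4. For participants already enrolled, report wear dates relative to randomisation and to the first session. Add a sensitivity analysis of follow-up accelerometry that adjusts for pre-randomisation PASE in place of any month-0 recording that overlaps treatment. Keep the planned analysis as the main one, for the reason in step 4 of the working.

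The cost is about one to two weeks' delay to randomisation, or to the first appointment under option 2, for the subsample of about 90, plus one extra item before randomisation. Under option 1 units can no longer be assigned by arm, so the split would be close to 30 per group rather than fixed at it.
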